### Study design

We propose a phase II, multicentre Bayesian trial. A total of 155 patients will be randomized in a 1:3 ratio to CL-RT (39 patients) or VC-RT (116 patients). Patients will be stratified by tumor stage (T1a/T1b) and by site (Fig. 1). This study, which is registered on clinicaltrials.gov (NCT03759431), will include tertiary, academic hospitals in Canada and the United States. One dose and fractionation regimen will be determined by each participating center and will have to be the same in both arms. The study is powered to compare LC of VC-RT compared to historical outcomes of CL-RT. The purpose of the randomization will be to generate data on secondary outcomes of voice impairment, dysphagia and quality of life as well as survival outcomes in the control arm.

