### Statistical considerations

According to previous experience, expected LC after CL-RT is estimated to be 92% [6, 8]. Assuming a non-inferiority margin of 8%, if LC in the VC-RT arm is ≥84% at 2-years, we will deem the VC-RT arm acceptable. With a sample size of 111 patients, over 82% power will detect a margin difference of 8%, at a target significance level of 0.05 using a one-sided, exact binomial test (NCSS-PASS 2005). The purpose of the randomization will be to generate currently unavailable data on secondary outcomes of voice impairment, dysphagia and quality of life in the CL-RT arm. Considering a 5% attrition rate, 155 patients will be randomized in a 1:3 ratio to CL-RT (39 patients) and VC-RT (116 patients) arms. Patients will be stratified by stage (T1a/T1b) and by institution.

An interim analysis will be conducted when 55 patients have a minimal follow-up of 6 months. We will monitor the efficacy endpoint using the Bayesian optimal phase 2 (BOP2) design [62]. Specifically, let *n* denote the interim sample size and *N* denote the maximum sample size. Let *p*_*eff*_ denote the probability of efficacy (response rate) and define the null hypothesis *H*_0_ : *p*_*eff*_ < 0.84, representing that the treatment is inefficacious. We will stop enrolling patients and claim that the treatment is not promising if
$$ \mathit{\Pr}\left({p}_{eff}\ge 0.84\mid data\right)<\lambda {\left(\frac{n}{N}\right)}^{\alpha }, $$where *λ* =0.95 and *α* =1 are design parameters optimized to minimize the chance of incorrectly claiming that an efficacious treatment is not promising (i.e., type II error) under the alternative hypothesis *H*_1_ : *p*_*eff*_ = 0.92, while controlling the type I error rate at 0.05 (i.e., the chance of incorrectly claiming that an inefficacious treatment is promising is no more than 5%). Assuming a Beta (0.84,0.16) prior distribution for *p*_*eff*_, if more than 10 patients among the 55 patients develop recurrences, the trial will be stopped in the interim analysis. Otherwise, the trial will be continued.

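### The printed interim limit (stop at 11 or more recurrences in 55) is one recurrence more lenient than the plan's own BOP2 formula gives when n and N both count VC-RT patients

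*Protocol article*

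**What the plan says.** The Statistical considerations section sets a single-arm test of VC-RT against a fixed rate: "if LC in the VC-RT arm is ≥84% at 2-years, we will deem the VC-RT arm acceptable". The planning rate is 92%, the margin is 8 percentage points, and 111 patients give just over 82% power "at a target significance level of 0.05 using a one-sided, exact binomial test".

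For the interim look, the same section prints a BOP2 rule: stop if Pr(p_eff ≥ 0.84 | data) < λ(n/N)^α, with λ = 0.95, α = 1 and a Beta(0.84, 0.16) prior. It says that λ and α "are design parameters optimized to minimize the chance of incorrectly claiming that an efficacious treatment is not promising" while the type I error is held at 0.05. It describes n as the interim sample size and N as the maximum sample size, and gives N no number. It then states the consequence: "if more than 10 patients among the 55 patients develop recurrences, the trial will be stopped in the interim analysis". In counts, that means stop at 11 or more and continue at 10.

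Three other places bear on what n and N count:

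- Analytic plan, and Data safety and monitoring board: both place the 55 interim patients in the experimental arm.
- Study design: the study is powered for VC-RT against historical CL-RT outcomes, and randomization serves the secondary outcomes.
- Study design, on numbers: "A total of 155 patients will be randomized in a 1:3 ratio to CL-RT (39 patients) or VC-RT (116 patients").

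**The concern.** The formula, its parameters, the prior and the resulting count are all printed, so the count can be checked directly. The monitored quantity is local control on VC-RT, the numerator n is 55 VC-RT patients, and the design sample size is 111 VC-RT patients. In the fraction n/N, both terms should count the same patients. On that reading the formula and the printed count give opposite decisions at exactly 10 recurrences.

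This is the only numeric early-stopping limit in the article. The Analytic plan says that the early look is there for safety, to detect a trend in local recurrence. The Discussion notes that salvage after a local recurrence is frequently total laryngectomy. A monitoring board that applied the formula and one that applied the count would disagree at 10 of 55.

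**Working it through.** **Inputs** (all from Statistical considerations unless noted): null rate 0.84; alternative 0.92; λ = 0.95; α = 1; prior Beta(0.84, 0.16); interim n = 55, VC-RT arm (Analytic plan; Data safety and monitoring board); 111 evaluable and 116 randomized to VC-RT; 155 in total, including 39 CL-RT (Study design).

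**Step 1. Reproduce the plan's design figure.** With 111 patients, the exact one-sided binomial test at 0.05 declares success at 100 or more controlled, i.e. at most 11 recurrences.

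- Type I error: Pr(X ≤ 11 | 111, 0.16) = 0.0464.
- Power: Pr(X ≤ 11 | 111, 0.08) = 0.823.

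The stated power of over 82% is reproduced.

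**Step 2. Apply the BOP2 formula at the final analysis.** At n = N the cut-off is 0.95. With N = 111 the posterior probability is 0.973 at 11 recurrences and 0.949 at 12, so success again means at most 11, with the same type I error and power. With N = 116 the final rule allows 12 recurrences, and the type I error is 0.057, above the stated 5%. N = 111 is therefore the value at which the formula and the design agree.

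**Step 3. Posterior at the interim.** With x recurrences in 55, the posterior is Beta(0.84 + 55 − x, 0.16 + x).

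| x | Pr(p_eff ≥ 0.84) |
|---|---|
| 9 | 0.504 |
| 10 | 0.362 |
| 11 | 0.240 |

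**Step 4. Interim cut-offs, 0.95 × 55/N.**

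| N | Cut-off | Formula stops at |
|---|---|---|
| 111 | 0.471 | 10 or more |
| 116 | 0.450 | 10 or more |
| 147 (155 less 5%) | 0.355 | 11 or more |
| 155 | 0.337 | 11 or more |

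**Step 5. Which N gives the printed count?** Ten recurrences must continue, so N > 0.95 × 55/0.3618 = 144.4. Eleven must stop, so N < 0.95 × 55/0.23997 = 217.7. Hence N runs from 145 to 217. Of the sample sizes stated in the article, only 155 lies in that range.

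**Step 6. Sensitivity to the prior.** Beta(1, 1), Beta(0.5, 0.5), Beta(0.92, 0.08), Beta(8.4, 1.6) and Beta(84, 16) give stopping at 9 or at 10 with N = 111 or 116, never at 11. Beta(0.84, 0.16) is thus not the reason for the mismatch.

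**Step 7. Consequences at N = 111** (success at most 11 recurrences, interim outcomes treated as final 2-year status).

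| | Printed count (≥ 11) | Formula (≥ 10) |
|---|---|---|
| Overall type I error | 4.64% | 4.63% |
| Overall power | 82.30% | 82.26% |
| Interim stop, true LC 84% | 25.8% | 38.4% |
| Interim stop, true LC 80% | 55.4% | 68.4% |
| Interim stop, true LC 92% | 0.4% | 1.1% |

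**Step 8. Allow for short follow-up.** The interim needs only 6 months' minimum follow-up, and the article gives no recurrence timing. Assume that a share s of 2-year recurrences is visible at the interim, so the recurrence probability is 0.16s when true local control is 84%.

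| s | Printed count (≥ 11) | Formula (≥ 10) |
|---|---|---|
| 100% | 25.8% | 38.4% |
| 75% | 6.0% | 11.7% |
| 50% | 0.4% | 1.1% |
| 25% | 0.001% | 0.006% |

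At true local control 80% and s = 50%, the figures are 1.9% and 4.4%.

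**The case against.** The strongest reply is that N has no number. If the maximum sample size is the trial total of 155, the printed count follows exactly and there is no arithmetic slip. That is right as arithmetic, but it moves the fault elsewhere: 55 VC-RT patients would be divided by a total that includes 39 CL-RT patients who contribute nothing to p_eff. The information fraction would be 55/155 = 35% instead of 55/111 = 50%. The count and the formula agree on that reading only because the numerator and denominator count different groups.

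A reader might go further and infer that the sponsor did use 155, or that 155 is the only value that works. The article supports neither. Any N from 145 to 217 gives the printed count, and a slip between ten-or-more and more-than-ten would explain the mismatch equally well.

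A second reply is that one count hardly matters. For the primary conclusion this stands: type I error and power move by 0.01 and 0.04 percentage points. The DSMB also reviews safety twice a year and can recommend suspension or termination, so the count is not the only protection.

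A third reply is that a stopping gap of 12.6 points at true local control 84% (38.4% − 25.8%) does not describe this interim. This also stands. That gap assumes complete 2-year outcomes for all 55 patients, and it shrinks to under one point if half of the recurrences are visible. Some patients will have more than 6 months' follow-up, but the share seen by then cannot be derived from the article.

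**Conclusion.** The point holds in a limited form. When n and N both count VC-RT patients, the printed formula stops at 10 or more of 55, and the printed count is one recurrence more lenient. This is true for N = 111 and for N = 116. It rests on reading N as the VC-RT arm, which the placement of the 55 in the experimental arm, the comparison with historical outcomes and the agreement of N = 111 with the stated power all support. Why the mismatch arose cannot be determined from the article.

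The practical effect is confined to a result of exactly 10 of 55, where the formula and the count give opposite decisions. It would be tempting to conclude that the primary analysis is compromised or that patients lose substantial protection. The calculations do not bear that out: the overall error rates are essentially unchanged, and the stopping probability at true local control 84% differs by 12.6 points only with complete 2-year data, and by about 0.7 points (0.4% v 1.1%) if half of the recurrences are seen. Severity: should fix.

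**What to change.** Give N a number in the Statistical considerations and say that it is the maximum number of evaluable VC-RT patients. N = 111 is the value that reproduces the stated power and keeps the type I error at 0.0464. Use that N for both the interim and the final cut-offs, and state there, as the Analytic plan already does, that the 55 are VC-RT patients.

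Then reconcile the printed count with the formula; at N = 111 the formula gives stopping at 10 or more. If the team means to keep the printed count, the printed formula or its parameters must be changed so that they produce it, with the operating characteristics shown. For instance, an exponent of 1.5 at N = 111 yields 11 or more, but the article states an exponent of 1.

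Inform the DSMB of the reconciled rule before the interim analysis. The cost is a one-line amendment and a note to the board. If the count moves to what the formula gives at N = 111, the loss of power is 0.04 percentage points (82.30% to 82.26%), and the chance of stopping a treatment with true local control of 92% rises from 0.4% to at most 1.1%.

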### Analytic plan

A Bayesian regression model [63, 64] will be used to compare the LC between the VC-RT and CL-RT arms at 2 years. The LC and OS time will be defined from end of RT date. The following recurrences will be considered LC: in field, field margin and within larynx. Local recurrences will be biopsy-proven when possible. Competing events will include local recurrence, regional/distant recurrence and death prior to recurrence. LC will be estimated using both competing risk and Kaplan -Meier (KM) analysis. The analyses will be conducted using SAS and R software. A Cox multivariable regression analysis will be used to determine factors predictive of LC, PFS and OS. Chi-squared test or Fisher’s exact test will be used to compare the difference in toxicity between arms. For the secondary endpoints of patient-reported outcomes (VHI-10, MDADI and MDASI-HN), trajectory trends of scores between/among arms over time will be explored using a generalized linear mixed model with a random effect of time. Appropriate adjustments for covariates will be considered.

There will be two planned analysis: 1) an interim analysis and, 2) a final analysis. The interim analysis will be done after 55 patients on the experimental arm have a minimum follow-up of 6 months. A short follow-up time of 6 months was chosen for the interim analysis for safety (i.e. for early detection of local recurrence trends). The trial may be interrupted early if VC-RT is deemed not promising on interim analysis. The final analysis will performed 2 years after accrual is completed.

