### Intervention

In both treatment arms, patients will be treated with a radical course of radiotherapy using a standard mild hypofractionation regimen of 5 fractions per week, over 4 to 6 weeks. For pragmatic reasons, each participating institution is allowed to use their standard of care dose and fractionation, but will have to be identical between the standard and experimental arms at each institution. Each center will provide, at time study entrance, what dose and fractionation will be used. This dose and fractionation will be the same for both arms and cannot change over the course of the study. The study is stratified by participating institution, which means that it will be stratified by dose/fractionation. In both treatment arms, a daily volumetric imaging method will be required for set-up verification, with match on the larynx.

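### Toxicity is to be compared between arms with an unstratified test although randomisation is stratified by T stage and site: a conservative choice that may give away some power on a secondary endpoint

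*Protocol article*

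**What the plan says.** Under Statistical considerations the protocol article states: "Patients will be stratified by stage (T1a/T1b) and by institution". The Intervention section adds what the institution stratum stands for: "The study is stratified by participating institution, which means that it will be stratified by dose/fractionation". The sample is small and unequal: "155 patients will be randomized in a 1:3 ratio to CL-RT (39 patients) and VC-RT (116 patients) arms".

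The Analytic plan then treats the between-arm comparisons in two ways.

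- **Toxicity.** A named two-by-two method, chi-squared or Fisher's "exact test will be used to compare the difference in toxicity between arms". No stratum enters it, and neither test can take a covariate.
- **The other outcomes.** Regression models with unprinted covariate lists. A Bayesian regression "will be used to compare the LC between the VC-RT and CL-RT arms at 2 years". For the time-to-event outcomes, "A Cox multivariable regression analysis will be used to determine factors predictive of LC, PFS and OS". The questionnaire scores are to be "explored using a generalized linear mixed model with a random effect of time", followed by "Appropriate adjustments for covariates will be considered".

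The toxicity sentence is therefore a stated method, not a detail left to an analysis plan. An analysis plan that followed it would run an unstratified test.

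**The concern.** Stratified randomisation removes between-stratum variation from the difference between arms. A pooled two-by-two test still counts that variation in its standard error. If the strata predict the outcome, the standard error is too large, the test rejects too rarely under the null, and power is lost.

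The article itself gives reason to expect that the strata predict toxicity. Site carries dose and fractionation, and may carry the choice between photons and protons. T stage decides whether one or both cords are in the target volume, and it changes the carotid dose goals. The Background links dose to laryngeal oedema, voice and carotid effects.

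At stake is a secondary endpoint, but a relevant one. The powered analysis uses the experimental arm alone, so the randomised control arm serves mainly the secondary outcomes. With 39 controls, power is scarce, and lower toxicity is the rationale for the smaller volume.

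**Working it through.** **1. The plan's own figure.** Primary test: n = 111, null 0.84, alternative 0.92, one-sided exact binomial at 0.05. The smallest number of locally controlled patients with exact type I error at or below 0.05 is 100. Then P(X ≥ 100 | 0.84) = 0.0464 and P(X ≥ 100 | 0.92) = 0.823. The stated power of over 82% reproduces. It uses neither the control arm nor the strata. The article states no type I error or power for toxicity, so no figure is contradicted there.

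**2. Mechanism.** Let R² be the share of outcome variance explained by the strata, with arms balanced within strata. The true variance of the arm difference is about (1 − R²) times what the pooled test assumes, so the true two-sided size is 2 × [1 − Φ(1.96 / √(1 − R²))].

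- R² = 0: 5.0%.
- R² = 0.05: 1.96 / 0.975 = 2.011, size 4.4%.
- R² = 0.10: 1.96 / 0.949 = 2.066, size 3.9%.
- R² = 0.15: 1.96 / 0.922 = 2.126, size 3.4%.

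The departure is always downward.

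**3. Simulated trials, strata = site × T stage.** From the article: 155 patients, 1:3, stratified by site and T stage. Assumed, because the article gives no figures: 5, 10 or 15 sites, permuted blocks of 4, 25% T1b, baseline toxicity log-odds −0.85 for size and 0.4 with odds ratio 0.35 for power, two-sided 0.05, 6,000 trials per setting. The strata effect is both the site SD on the logit scale and the T-stage log odds ratio. Ranges run over 5 to 15 sites; CMH is the Cochran-Mantel-Haenszel test.

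| Strata effect | Size, chi-squared | Size, Fisher | Size, CMH | Power, chi-squared | Power, CMH |
|---|---|---|---|---|---|
| 0 | 4.7–5.0% | 3.6–3.9% | 4.9–5.2% | 80–81% | 79–80% |
| 0.5 | 4.2–4.5% | 3.2–3.3% | 4.6–4.9% | 75–77% | 75–78% |
| 1.0 | 3.2–3.3% | 2.3–2.4% | 4.6–4.7% | 64–65% | 69–71% |
| 1.5 | 2.4–2.7% | 1.6–1.8% | 4.9–5.4% | 49–50% | 62–63% |

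Paired differences in power, CMH minus chi-squared, for 5, 10 and 15 sites:

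- effect 0: −0.6, −1.2, −2.6 points;
- effect 0.5: +1.5, +0.5, −1.0;
- effect 1.0: +6.1, +6.2, +4.9;
- effect 1.5: about +13 in each.

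Fisher's test is already conservative with no strata effect, and its power is 3 to 5 points below chi-squared throughout.

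**4. Simulated trials, strata = site only.** With 6 to 10 sites and blocks of 4, chi-squared size is 4.0–4.5%, 3.6–3.8% and 3.2–3.9% at site SDs of 0.5, 0.8 and 1.0. The site-stratified test stays near 5%. Its gain in power is about 1 point at 0.5, 3 to 4 at 0.8 and 5 to 7 at 1.0, with essentially no loss at 0. One setting at SD 0.8 (control toxicity 50%, odds ratio 0.4, T1b odds ratio 2) goes from 57.5% to 61.0%.

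**5. What these SDs mean.** Around a 50% toxicity rate, 95% of sites lie between logit⁻¹(±1.96 × SD): 27–73% at SD 0.5, 17–83% at 0.8 and 12–88% at 1.0.

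**The case against.** The strongest reply is that the loss is not shown to be material. The article gives no number of sites, block size, T1b share, toxicity rate or between-site spread. An SD of 1.0 means site rates from 12% to 88%, which is wide for centres that share mild hypofractionation, common planning criteria and daily image guidance on the larynx. At 0.5 the gain is about 1 point, and fine strata can even cost a little. This stands: the size is conditional on assumptions, and the modest end is plausible.

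Four stronger readings are tempting, and the article does not support them.

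- **That no between-arm analysis uses the strata.** The local-control, Cox and questionnaire analyses are regression models with open covariate lists, and the Analytic plan says adjustment will be considered. They do not commit to the strata, but they do not exclude them, and such lists commonly sit in the full protocol or analysis plan.
- **That false positives are inflated.** The error runs only in the conservative direction.
- **That the pooled comparison is confounded by regimen.** The Discussion's stated reason for stratifying is balance of regimens between arms, and stratified randomisation delivers that. The pooled comparison is a valid marginal one.
- **That the primary conclusion is affected.** It rests on one arm against a fixed 84%.

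What the reply does not remove is that the toxicity test is fixed in the text, is unstratified, and cannot be adjusted by the later remark on covariates.

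**Conclusion.** The point holds for the toxicity comparison only. The fixed test ignores the randomisation strata. If site or T stage predicts toxicity, its true type I error is below the nominal 5% and it loses power: about 1 point at a site SD of 0.5, 3 to 4 at 0.8, 5 to 7 at 1.0, and none if the strata do not matter. The direction follows from the design. The size rests on the assumed site heterogeneity, number of sites, block size and toxicity rates. This is an improvement to a secondary analysis, not an error that threatens the trial's conclusion.

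**What to change.** In the Analytic plan, replace the pooled toxicity test with a Cochran-Mantel-Haenszel test stratified by site and T stage, using an exact version for rare events. State in advance how sparse sites are pooled, with dose regimen as the natural grouping. Report the stratified odds ratio or risk difference with its interval; the risk difference suits readers who prefer an absolute effect. Preferably also commit to T stage and site as covariates in the local-control, survival and questionnaire comparisons, so that the open remark on adjustment becomes a rule.

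The cost is wording; no patients or data are added. The one downside is that a stratum with patients in only one arm contributes nothing. With 39 controls over an assumed 6 to 10 sites there are about 39/10 = 3.9 to 39/6 = 6.5 controls per site, so full site × stage strata can be thin. If the strata turn out not to be prognostic, such fine strata cost at most about 1 to 3 points of power. Pooling by regimen should limit this, and stratifying by site alone cost essentially nothing in the simulated trials.

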## Methods/design

### Study objectives

The objective of this trial is to assess the efficacy and safety of VC-RT, compared to CL-RT, in T1N0 glottic squamous cell carcinoma.

Primary endpoint:
Local control at 2-year after the end of RT.

*Local control will be defined as absence of biopsy proven recurrence within the larynx.*

Secondary endpoints:
Patient-reported outcomes including dysphagia, voice impairment, and symptom burden.Acute and late toxicity radiation-induced toxicityOS and progression free survival (PFS)Acoustic and objective measures of voice analysis using the Consensus Auditory-Perceptual Evaluation of Voice.

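### The interim stopping limit is calibrated to complete 2-year outcomes but applied from 6 months of follow-up, which weakens its ability to stop for harm by an amount that depends on unstated accrual and recurrence timing

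*Protocol article*

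**What the plan says.** Study objectives sets the primary endpoint as "Local control at 2-year after the end of RT". Statistical considerations ties the acceptability limit to the same time: "Assuming a non-inferiority margin of 8%, if LC in the VC-RT arm is ≥84% at 2-years, we will deem the VC-RT arm acceptable". The value 0.84 then becomes the null in the Bayesian optimal phase 2 (BOP2) rule, with 0.92 as the alternative, a Beta(0.84, 0.16) prior, λ = 0.95 and α = 1. The rule is reduced to a fixed count: "if more than 10 patients among the 55 patients develop recurrences, the trial will be stopped in the interim analysis"; at or below that count the trial goes on.

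The timing is in Analytic plan: "The interim analysis will be done after 55 patients on the experimental arm have a minimum follow-up of 6 months". That section explains the short follow-up as a safety measure, meant to pick up recurrence trends early. The section on the data safety and monitoring board (DSMB) repeats the 55-patient, 6-month look and adds a safety review twice a year, for which it states no numerical limit.

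The article gives no accrual rate. On recurrence timing, the Discussion says only that most local recurrences fall within 2 years; no share by 6 or 12 months is given.

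**The concern.** The null, the alternative and the limit are all 2-year quantities, and the count of 10 is what the posterior gives when 55 outcomes are fully known. At the interim some or all of the 55 will have been followed for less than 24 months. Nothing in the rule allows for this, so every patient who has not yet recurred enters as a success.

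The effect runs in one direction: the observed count is at or below what it would be with full follow-up, and the chance of stopping falls with it. A look placed early in order to protect patients is thus paired with a limit scaled to a later time. The Discussion notes that salvage after local recurrence is frequently total laryngectomy, so lost sensitivity in this rule matters to patients during the trial, even though it leaves the final test intact.

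**Working it through.** **Inputs.** From Statistical considerations: null 0.84, alternative 0.92, prior Beta(0.84, 0.16), λ = 0.95, α = 1, 55 patients at the interim, stop at 11 or more recurrences, 111 evaluable and 116 randomized VC-RT patients, 155 in total. From Analytic plan: minimum follow-up 6 months. Accrual time of the 55 and the recurrence-time curve are not in the article and are assumed below over a range.

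**1. The plan's own power.** The article states "With a sample size of 111 patients, over 82% power will detect a margin difference of 8" (per cent), "at a target significance level of 0.05 using a one-sided, exact binomial test". With n = 111, 100 or more controlled patients are needed: P(Bin(111, 0.84) ≥ 100) = 0.0464 and P(Bin(111, 0.92) ≥ 100) = 0.823. The stated figure is reproduced.

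**2. The interim count.** With x recurrences among 55 complete outcomes the posterior is Beta(0.84 + 55 − x, 0.16 + x). Pr(p ≥ 0.84) is 0.362 at x = 10 and 0.240 at x = 11. The cut-off is 0.95 × 55/N:
- N = 111: 0.471, so the formula stops at 10.
- N = 116: 0.450, so it stops at 10.
- N = 155: 0.337, so it stops at 11.

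The written count is therefore a complete-data limit. It matches the formula only if N is the total of both arms; for the VC-RT arm's own N it is one recurrence too lax.

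**3. Stopping with complete 2-year data.** P(Bin(55, 1 − LC) ≥ 11) is 25.8% at LC 84%, 80.1% at 76% and 96.6% at 70%.

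**4. Stopping with partial follow-up, constant hazard.** The chance that a patient followed for t months has recurred is q(t) = 1 − LC^(min(t, 24)/24). With all 55 at exactly 6 months and LC 70%, q = 1 − 0.70^0.25 = 0.085, giving 55 × 0.085 = 4.7 expected recurrences. For even accrual over A months, q(t) is averaged over t from 6 to 6 + A. P(11 or more of 55) is then approximately:

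| True 2-year LC | All at 6 mo | A = 12 | A = 18 | A = 24 | A = 36 | Complete |
|---|---|---|---|---|---|---|
| 84% | <0.1% | 0.5% | 2% | 5% | 10% | 26% |
| 76% | 0.1% | 8% | 23% | 38% | 54% | 80% |
| 70% | 0.6% | 27% | 53% | 71% | 84% | 97% |

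**5. Stopping if recurrences come early.** Assume half of the 2-year failures occur by 6 months and 80% by 12. With all at exactly 6 months, q = 0.5 × (1 − LC), and the chance of stopping is 6% at LC 76% and 19% at LC 70%. At LC 70%, even accrual over 12, 18, 24 or 36 months gives about 72%, 82%, 88% or 92%.

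In every scenario the chance of stopping is below the complete-data figure.

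**The case against.** Six months is a minimum, so the case of all 55 at exactly 6 months is a floor that would need near-simultaneous entry. If the 55 took 36 months to accrue evenly, median follow-up would be 6 + 18 = 24 months and the rule would stop an arm with LC 70% about 84% of the time. With early failures it would do so 72% of the time or more even after 12-month accrual. A reader might infer that the rule rarely stops for a clearly harmful arm. The article does not support that as a general statement, because it gives neither accrual rate nor recurrence timing.

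A reader might also infer that the design's stated error rates are wrong. They are not shown to be. The article gives no interim stopping probability, and a stopping look that is too lax does not inflate the final type I error, which stays at about 0.046.

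Finally, the DSMB reviews cumulative safety data twice a year and may recommend suspension or termination. That is a real safeguard, but a partial one: the only numerical limit stated for recurrences is the one at issue.

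These points limit the size of the claim. They leave the mismatch between limit and follow-up as it is.

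**Conclusion.** The mismatch stands. A count derived from a 2-year null with 55 complete outcomes is applied from 6 months of follow-up without adjustment, so the rule is less sensitive to harm than the same count would be with complete data. The loss is conditional. At a true LC of 70% under constant hazard it ranges from near-total (0.6% against 97%) to modest (84% against 97%), depending on how long the 55 take to accrue; early recurrences shrink it further. What is lost is protection during the trial; the validity of the final analysis is unaffected. It should be fixed before the interim. The written count and the stated formula also need to be reconciled, since they agree only with N = 155.

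**What to change.** Keep the look at 55 VC-RT patients with 6 months' minimum follow-up, and replace the fixed count by the same posterior with partial credit. For each recurrence-free patient let w = min(follow-up/24 months, 1), or a weight from a pre-specified recurrence-time curve. With e recurrences, use Beta(0.84 + Σw, 0.16 + e), effective sample size n = e + Σw, and stop if Pr(p ≥ 0.84) < 0.95 × n/N. State which N is meant, and report stopping probabilities over a range of accrual times and recurrence curves.

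With N = 111 and constant hazard, for accrual over 12, 18 and 24 months:
- LC 70%: stopping becomes about 81%, 89% and 94%. Part of this gain comes from the formula's limit of 10, since 10 or more without weighting already gives about 40%, 67% and 81%.
- LC 84%: about 17%, 22% and 30%.
- LC 92%: about 1%.

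The follow-up/24 weights assume roughly even timing. Under the early-failure pattern in the working, and with accrual of 24 months or less, the chance of wrongly stopping a 92% arm rises to about 3% to 7%, and stopping at LC 84% to about 45% to 50%. That is the reason to offer a pre-specified curve as an alternative and to show the range.

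The cost is a recalculation and revised wording of the interim rule for the DSMB; no extra patients, visits or delay are needed.

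### The final analysis is dated from end of accrual, not end of RT, so the last patients fall short of 24 months; the stated power and type I error, correct at 111 evaluable patients, shift at nearby numbers

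*Protocol article*

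**What the plan says.** - **Endpoint.** Study objectives (Protocol article) sets the primary endpoint as "Local control at 2-year after the end of RT". The Analytic plan also counts local control (LC) time from the end-of-RT date.
- **RT duration.** Intervention gives a course of 4 to 6 weeks.
- **Analysis date.** Analytic plan: "The final analysis will performed 2 years after accrual is completed".
- **Sizing.** Statistical considerations takes 92% as the LC to be expected with CL-RT and 84% as the lower limit for VC-RT. On power it says: "With a sample size of 111 patients, over 82% power will detect a margin difference of 8" (percentage points). The test named is an exact binomial, one-sided at the 0.05 level.
- **Attrition.** The randomised numbers are 39 for CL-RT and 116 for VC-RT: "Considering a 5% attrition rate, 155 patients will be randomized in a 1:3 ratio".
- **BOP2.** The same section gives λ = 0.95, α = 1 and a Beta(0.84, 0.16) prior. It stops at the interim if more than 10 of 55 patients recur, and states a type I error of no more than 5%.

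**The concern.** The endpoint clock starts at end of RT and the analysis clock at end of accrual. A patient randomised on the last day of accrual still has planning and 4 to 6 weeks of RT ahead, so the 24-month post-RT visit falls after the analysis date.

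This matters more than a few weeks of follow-up usually would, because the quoted power and type I error belong to rules that count patients with a known 2-year status. Such rules are discrete: the permitted number of failures moves in whole steps, so a small change in the evaluable number can move power or type I error by several points. The attrition allowance, 116 − 111 = 5 patients, leaves little room. At stake is either a lower chance of recognising an acceptable VC-RT arm, or a higher chance than stated of endorsing one whose true LC is only 84%.

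**Working it through.** **1. The date.** Let g be the time from randomisation to end of RT. Anyone randomised within g of the end of accrual has less than 24 months after RT at the analysis. RT alone makes g at least 4 to 6 weeks, so with accrual continuing to the end the number is above zero. Its size needs two figures that the article does not give. With even accrual:

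VC-RT patients short of 24 months = 116 / (accrual in months) × g

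| Assumed accrual | g = 1 month | g = 2.5 months |
|---|---|---|
| 2 years | 4.8 | 12.1 |
| 3 years | 3.2 | 8.1 |
| 4 years | 2.4 | 6.0 |
| 5 years | 1.9 | 4.8 |
| 6 years | 1.6 | 4.0 |

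That is roughly 2 to 12 patients. Taking 5% attrition from the remainder leaves about 99, (116 − 12.1) × 0.95, to 109, (116 − 1.6) × 0.95.

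**2. Attrition alone.** 111 / 0.95 = 116.8, so 117 would be needed; 116 × 0.95 = 110.2, so about 110 are expected.

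**3. The plan's own figure.** Exact one-sided test: the failure limit f is the largest with P(X ≤ f | failure rate 0.16) ≤ 0.05, and power is P(X ≤ f | failure rate 0.08). At n = 111, f = 11, type I error 0.0464, power 0.823. The stated power of over 82% reproduces.

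**4. Neighbouring numbers.** For BOP2, success at the end requires Pr(p ≥ 0.84 | data) ≥ 0.95 with the stated prior, N is set to the evaluable n, and the interim limit is the stated 10 of 55.

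| n | Exact: limit | Type I | Power | BOP2: limit | Type I | Power |
|---|---|---|---|---|---|---|
| 103 | 10 | 0.0476 | 0.799 | 10 | 0.0476 | 0.799 |
| 104 | 10 | 0.0439 | 0.791 | 11 | 0.0795 | 0.873 |
| 108 | 10 | 0.0313 | 0.754 | 11 | 0.0587 | 0.845 |
| 109 | 10 | 0.0287 | 0.745 | 11 | 0.0544 | 0.838 |
| 110 | 10 | 0.0263 | 0.735 | 11 | 0.0503 | 0.831 |
| **111** | **11** | **0.0464** | **0.823** | **11** | **0.0464** | **0.823** |
| 112 | 11 | 0.0429 | 0.815 | 12 | 0.0761 | 0.888 |
| 113 | 11 | 0.0395 | 0.807 | 12 | 0.0708 | 0.882 |
| 116 | 11 | 0.0309 | 0.783 | 12 | 0.0567 | 0.864 |

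At n = 110, 11 failures would give an exact type I error of 0.0503, just over 0.05. The exact test must therefore drop to 10, which costs about 9 points of power.

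**5. Random attrition.** If each of 116 patients is lost independently with probability 0.05, P(n < 111) = 0.53, P(n = 111) = 0.17, and average exact-test power is about 78%.

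**6. Low end.** At 99 to 102 evaluable, reached only under the shortest accrual or the longest gaps in step 1, the exact limit is 9 and power is 73.2% falling to 70.1%. At 101 and 102 the BOP2 rule narrowly misses both targets (type I error 0.056 and 0.052; power 81.6% and 80.8%).

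**The case against.** Much of the opposing case stands.

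- **The stated figure is right.** Power is claimed for 111 patients and reproduces there. Saw-tooth power is common to exact binomial designs, and 116 against 117 is rounding. This is not a sample-size error.
- **A reader might infer that power and type I error both fail at the expected 110.** They do not. The exact test has a type I error of 2.6% and loses only power. BOP2 keeps 83.1% power and exceeds 5% by about 0.03 points. At no n from 103 to 116 does either rule miss both targets.
- **A reader might infer that 111 is the only number that works.** Among numbers up to 116 it is the only one with exact-test power above 82%, but 112 and 113 give 81.5% and 80.7%, a minor departure. At 118 both targets are met again, though 116 randomised cannot reach it.
- **The late patients are not simply lost.** The Analytic plan estimates LC by Kaplan-Meier and competing-risk methods, which would censor them near 24 months and use nearly all their follow-up. The 24-month visit is a study visit, so the data are late, not absent. The loss applies to the binary rules, but those are the rules from which the quoted power and type I error come.
- **The BOP2 figures depend on applying 0.95 to the realised n.** The full protocol or SAP, not shown here, may fix the failure count instead.
- **The number of late patients is assumed.** The article does not show that it uses up the attrition allowance.

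**Conclusion.** The timing conflict is certain from the article's own text: the analysis date does not give the last-accrued patients the 24 months after RT that the primary endpoint needs. Its size, roughly 2 to 12 VC-RT patients, rests on assumed accrual of 2 to 6 years and a gap of 1 to 2.5 months.

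The quoted operating characteristics are correct at 111 but sensitive to the evaluable number, and the plan's own attrition points to about 110. Under the exact test, type I error holds and power is 73.5% at 110, 74.5 to 79.1% at 104 to 109, and 78.3 to 81.5% at 112 to 116. Under the BOP2 cut-off applied to the realised number, power holds over 104 to 116, while type I error is 5.03% at 110 (trivial), 5.4 to 7.9% at 104 to 109, and 5.7 to 7.6% at 112 to 116. One claim weakens under each rule. The point should be corrected, but it does not invalidate the design.

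**What to change.** 1. **Date.** Time the final analysis to when the last randomised patient has reached the 24-month post-RT assessment, or has died or been lost. Cost: readout about 2 to 3 months later.
2. **Failure limit.** Pre-specify the maximum number of failures by evaluable n so that type I error stays at or below 0.05: at most 10 for n = 103 to 110, at most 11 for n = 111 to 117. Cost: wording, and at n = 110 about 9 points of power compared with allowing 11 failures.
3. **Power statement.** Restate power as about 74 to 82% for n = 103 to 116, with 82% applying at 111. With the date corrected, only attrition reduces the number, and falling below 103 is then very unlikely at 5% loss. Cost: a slightly less favourable stated figure.
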